## Abstract

**Background:**

The prevalence of overweight is increasing and its consequences will cause a major public health burden in the near future. Cost-effective interventions for weight control among the general population are therefore needed. The ALIFE@Work study is investigating a novel lifestyle intervention, aimed at the working population, with individual counselling through either phone or e-mail. This article describes the design of the study and the participant flow up to and including randomisation.

**Methods/Design:**

ALIFE@Work is a controlled trial, with randomisation to three arms: a control group, a phone based intervention group and an internet based intervention group. The intervention takes six months and is based on a cognitive behavioural approach, addressing physical activity and diet. It consists of 10 lessons with feedback from a personal counsellor, either by phone or e-mail, between each lesson. Lessons contain educational content combined with behaviour change strategies. Assignments in each lesson teach the participant to apply these strategies to every day life.

The study population consists of employees from seven Dutch companies. The most important inclusion criteria are having a body mass index (BMI) ≥ 25 kg/m^2 ^and being an employed adult.

Primary outcomes of the study are body weight and BMI, diet and physical activity. Other outcomes are: perceived health; empowerment; stage of change and self-efficacy concerning weight control, physical activity and eating habits; work performance/productivity; waist circumference, sum of skin folds, blood pressure, total blood cholesterol level and aerobic fitness. A cost-utility- and a cost-effectiveness analysis will be performed as well.

Physiological outcomes are measured at baseline and after six and 24 months. Other outcomes are measured by questionnaire at baseline and after six, 12, 18 and 24 months.

Statistical analyses for short term (six month) results are performed with multiple linear regression. Analyses for long term (two year) results are performed with multiple longitudinal regression. Analyses for cost-effectiveness and cost-utility are done at one and two years, using bootstrapping techniques.

**Discussion:**

ALIFE@Work will make a substantial contribution to the development of cost-effective weight control- and lifestyle interventions that are applicable to and attractive for the large population at risk.

## Background

As is the global trend, more than 5.6 million adults in the Netherlands (i.e., 46.1% of the population of 20 years and older) are overweight and numbers are still rising [1]. Overweight is defined as having a body mass index (BMI) of 25 or higher. It is a risk factor for a range of health problems, most notably those related to the metabolic syndrome. This syndrome is characterised by abdominal adiposity and several associated metabolic anomalies like insulin resistance, dyslipidaemia and hypertension. These metabolic changes are related to the development of coronary heart disease and type 2 diabetes mellitus. The growing prevalence of overweight and the increase in severity will result in an increase in these diseases. We have to look at ways to turn this tide.

Research shows that intentional weight loss in overweight people with symptoms of the metabolic syndrome, produces a significant improvement in these symptoms and reduces the risk for developing diabetes [2-4]. Reduction in overall mortality as a result of intentional weight loss still needs to be established [5-7], but research shows that maintaining a normal BMI during adulthood protects against diabetes and cardiovascular disease [4]. Therefore, preventing weight gain is crucial in both people who are already overweight, as well as in those who are at risk for becoming overweight.

Overweight develops when the energy balance between physical activity and foods eaten, is generally positive [8]. Prevention of weight gain should concentrate on restoring this balance by increasing physical activity and improving quality of diet. In those seeking weight loss, a negative energy balance should be achieved. Both an increase in physical activity and a well balanced diet have positive effects by themselves. Physical activity reduces blood pressure, improves lipid profiles and protects against cardiovascular disease, type 2 diabetes and certain types of cancer [9]. A diet rich in fruit, vegetables and unsaturated fatty acids helps to lower blood pressure and blood total cholesterol, and prevents against the development of cardiovascular diseases [10]. Improvement of physical activity and diet therefore not only has positive effects on weight control, but also contributes to the amelioration of risk factors for coronary heart disease and type 2 diabetes mellitus. Weight control (i.e., weight loss, maintenance of lost weight and prevention of weight gain) interventions should promote these lifestyle changes.

While there is consensus on the incorporation of both diet and physical activity for weight control, less is known about how these behaviours can be sustainably changed. Most research in the field of weight control has concerned weight loss and to a lesser extent maintenance of lost weight. Little research has been directed towards prevention of weight gain and effective interventions still need to be determined [11]. Behavioural and cognitive behavioural therapies are commonly used for weight loss interventions [12]. They facilitate better maintenance of weight loss than other interventions. These therapies can be used either in a group approach as well as in individual treatment. In both approaches, multiple visits to a treatment centre are required. This is demanding for both the patient as well as the health care system and makes this mode of delivery not well suited for the large section of the population that needs to be reached. New approaches are therefore necessary. Two studies in the United States show that distance counselling programmes (i.e., personal coaching by mail, phone or e-mail) based on behavioural principles can be successful in producing weight loss [13,14]. Distance counselling promises to be cheaper and more accessible than traditional treatments. However, effects on weight maintenance and prevention of weight gain, changes in diet and physical activity, changes in metabolic risk factors and cost effectiveness still have to be established. The ALIFE@Work trial is designed to study these outcomes. This trial is carried out in a working population. Increasing numbers of employees have a sedentary profession and are therefore at risk of developing overweight, or are already overweight. Research shows that productivity losses due to overweight can amount to 10% [8]. Offering distance counselling to the working population might be a feasible and cost-effective way to reach a large group of those in need to change their lifestyle.

The main objective of the ALIFE@Work study is to evaluate, among an overweight working population, the effectiveness of a lifestyle intervention programme on body weight, physical activity and eating habits. Secondary objectives of this study are 1) to compare the effectiveness of the use of two different communication technologies, i.e., telephone and internet, and 2) to evaluate the cost-effectiveness of this lifestyle programme. In this article we describe the design of the study and the participant flow up to, and including randomisation.

## Methods/Design

ALIFE@Work is a randomised controlled trial with a two-year follow-up. Randomisation takes place to three groups: to a control group (control) and to an intervention programme either counselled by phone (phone), or counselled by email (internet). The recruitment and data collection for this study started in January 2004. Data collection will continue until September 2006.

The study design, procedures and informed consent form were approved by the Medical Ethics Committee of the VU University Medical Center (under number 03/193), and all participants provided written informed consent.

### Study population

Participants are employees of seven different companies in the Netherlands, including two IT-companies, two hospitals, an insurance company, the head office of a bank and a police force. Of the approximately 21,000 employees working at these companies about 40%, i.e. 8,400, were estimated to be overweight. All 21,000 employees were approached per company, through an invitational letter and a screening questionnaire. This was done in six months time, with an interval of three weeks to one month between the companies. The screening questionnaire included demographic questions and questions on body weight and body height.

### Inclusion & exclusion criteria

Inclusion criteria of the study were: 1) BMI ≥ 25 kg/m^2^, 2) paid employment of at least 8 hours a week, 3) adequate knowledge of the Dutch language, 4) access to internet and skilled in using it, 5) at least 18 years of age. Employees were excluded for the following reasons: pregnancy, diagnosis or treatment of cancer, any other disorder that makes physical activity impossible.

### Sample size

A power calculation was carried out for the main outcome variable, i.e. weight change. Calculations were made for a comparison between two equal size groups. Power calculation for weight change was carried out for three levels of power, namely 80%, 85% and 90%. The standard deviation (SD) for two-year weight loss was expected to be 6.8 kg, based on prior weight treatment studies [15,16]. Calculations showed that differences in mean two-year weight loss of about 1.4 kg between conditions will be detectable with 90% power in two-tailed tests with a significance level of 0.05 for a sample of 500 employees in each group. The sample size for the study was therefore determined at 1500.

### Randomisation

Randomisation took place at an individual level. After baseline measurements, the employee was randomised to one of the three study groups and either to a group receiving basic weight measurements (80% of each study group) or to a group receiving additional measurements (20% of each study group). This two-step randomisation meant that there were six groups an employee could be assigned to. Randomisation to these six groups was done by block randomisation, with each block containing 15 allocations. A computerized random number generator drew up an allocation schedule. An administrative assistant put the group allocation in opaque sealed envelopes, numbered 1 to 1,500. These envelopes were taken to the locations of the baseline measurements and opened in the given order. The researchers were blinded for the allocation schedule, but were not blinded for allocation after randomisation. The participants were, in consequence of the nature of the intervention, not blinded for allocation after randomisation. Employees were not allowed to change groups after randomisation.

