### Participant flow

The study design and participant flow (achieved at recruitment closure and brought up to closure of the baseline measurement period, August 2004) are shown in Figure 1.

Out of a total of approximately 21,000 employees, 4,619 returned the screening questionnaire. Of these, 2,615 were eligible and had no objections to receiving further information. They received an information brochure in which the study protocol was clearly described. Employees were free to further inquire about the study without any engagement. 1,454 employees were willing to participate and applied in time. They were all individually invited for a first appointment in which the basic measurements body weight and body height were assessed by the researchers. From these measurements, BMI was calculated. Those with a BMI lower than 25 kg/m^2^, which was the case for nine employees, were excluded. One employee became pregnant between screening and baseline measurements and was also excluded. One employee withdrew before randomisation. 57 employees did not show up for the baseline measurements. Therefore, 1,386 employees were randomised to the two intervention conditions (phone group N = 462, internet group N = 464), or to the control group (N = 460). Within these groups a number of subjects received additional measurements as follows: phone group N = 91, internet group N = 93 and control group N = 92. A second appointment was arranged within one week after randomisation, to perform these measurements. In each group a few employees were unable to attend the additional measurements: five out of the phone group, two out of the internet group, and ten out of the control group.

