#### Physiological outcome measures

For a random sample of each group, several additional physiological measurements are assessed in the following order: waist circumference, sum of skin folds, blood pressure, total blood cholesterol, and aerobic fitness. They are all done according to standardized protocols and take approximately 45 minutes per session.

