##### Sum of skin folds

According to the method of Weiner and Lourie [22] the following four skin folds are measured twice with a Harpenden caliper (HSK-BI; Baty International, Burgess Hill, UK) up to the nearest 0.1 mm and on the right side of the body: sub scapular, suprailiac, triceps and biceps. In case the two measurements of a fold differ more than 1.0 mm, the skin fold is measured a third time. Next, for each skin fold, a mean value of the measurements is computed and the four skin folds are added up.

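### Researchers are unblinded after randomisation and no masked assessor is described for skin folds and waist, which leaves an avoidable detection bias in these sub-sample outcomes

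*Protocol article*

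**What the plan says.** All places are in the protocol article.

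- **Randomisation:** "The researchers were blinded for the allocation schedule, but were not blinded for allocation after randomisation". Participants are also unblinded. The nature of the intervention is given as the reason for participants; no reason is given for researchers.
- **Physiological outcome measures:** a random 20% of each arm has waist, skin folds, blood pressure, cholesterol and fitness measured. On procedure the section says only: "They are all done according to standardized protocols and take approximately 45 minutes per session". It does not say who measures or what that person knows.
- **Waist circumference:** two manual tape readings, averaged.
- **Sum of skin folds:** two caliper readings at each of four sites, with this check: "In case the two measurements of a fold differ more than 1.0 mm, the skin fold is measured a third time". Then, "for each skin fold, a mean value of the measurements is computed and the four skin folds are added up".
- **Participant flow:** for the sub-sample baseline, "A second appointment was arranged within one week after randomisation, to perform these measurements". Allocation therefore already existed when these baseline readings were taken.
- **Discussion:** waist and skin folds are included because weight and BMI are associated with adiposity without measuring it directly.

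**The concern.** The article does not leave the blinding of researchers open. It states that they are unblinded after allocation, and nothing later describes a separate or masked assessor. For weight on a digital scale this matters little. A caliper reading depends on the exact site, the pinch and the moment of reading, and a tape reading depends on position and tension. An assessor who expects the counselled participants to have lost fat can shift such readings slightly without intending to.

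A shift of that kind becomes a between-arm difference in the measures meant to show an effect on adiposity, and the analysis cannot separate it from a treatment effect afterwards. The only reading-quality check described for skin folds is the third-reading rule, which compares one reading with another by the same procedure. None is described for waist beyond averaging two readings.

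**Working it through.** **The plan's own figure.** The only power calculation (Sample size section) is for weight: n = 2(1.96 + 1.2816)² × 6.8² / 1.4² ≈ 496 per group, against 500 stated. Power at 500 is 90.2%. The figure reproduces and is not in dispute. No figure is given for skin folds.

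**Inputs from the article.** Sub-sample attenders at baseline (Participant flow): phone 91 − 5 = 86, internet 93 − 2 = 91, control 92 − 10 = 82. The contrast is both intervention arms combined against control (Outcome measures section): 86 + 91 = 177 v 82. Four folds are summed.

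**Assumptions not in the article.** The SD of change in the four-fold sum is taken as 10, 15 or 20 mm. The bias is taken as 0.5 mm per fold in one direction, so 4 × 0.5 = 2 mm on the sum, present in the change score of one comparison group and not the other.

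**Step 1: does the third-reading rule limit such a bias?** Let the two readings be t + b + e₁ and t + b + e₂, with true value t, bias b and reading errors e₁ and e₂. Their difference is e₁ − e₂, so b drops out. In a simulation with an assumed within-reader SD of 0.5 mm, a third reading was triggered in about 16% of cases whether b was 0, 1 or 3 mm. The rule checks repeatability only.

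**Step 2: effect on the test.** SE = SD × √(1/177 + 1/82) = SD × 0.1336. With no true effect and a shift δ in the mean change, P(p<0.05) = Φ(δ/SE − 1.96) + Φ(−δ/SE − 1.96).

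| Assumed SD of change | SE | Shift that alone reaches p = 0.05 (1.96 × SE) | P(p<0.05), δ = 2 mm | P(p<0.05), δ = 1 mm |
|---|---|---|---|---|
| 10 mm | 1.34 mm | 2.62 mm | 32% | 12% |
| 15 mm | 2.00 mm | 3.93 mm | 17% | 8% |
| 20 mm | 2.67 mm | 5.24 mm | 12% | 7% |

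For SD 10: 2/1.336 = 1.497, and Φ(1.497 − 1.96) = Φ(−0.463) ≈ 0.32; the second term is negligible. The last column is roughly what remains if the 2 mm bias acts in only half of the participants, for example because the arm is known for half. With 30% loss to follow-up (124 v 57), the 2 mm column becomes 24%, 13% and 10%.

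**Step 3: does the bias survive in a change score?** If the same arm-related bias is present at baseline and follow-up, it cancels. The sub-sample baseline falls within a week after randomisation, and both programmes start about two weeks after it (Phone intervention and Internet intervention sections). An expectation that treated participants have lost fat therefore belongs to the follow-up visits, so cancellation cannot be assumed. Nor is there a pre-allocation reading of these outcomes to serve as an anchor.

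**The case against.** The strongest reply is that the article never says skin folds and waist are measured unmasked. That is correct. A reader might also take the Participant flow statement that "basic measurements body weight and body height were assessed by the researchers" as evidence about the assessors, but it concerns the visit before randomisation, when there was no arm to know. It says nothing about who holds the caliper later. What stands against the reply is that the researchers' unblinded status is stated outright and no masked assessor is mentioned.

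A second reply is that staff could hardly remember the arms of 276 sub-sample members after six or 24 months, so a full bias is unlikely. This has force and is why the percentages are illustrative. It holds only if lists and forms do not show the arm and participants do not reveal it, and the article settles neither.

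Third, some separation may already exist: questionnaires go to the home address, and counselling is done by four counsellors with their own management system. That makes the remaining step smaller but does not replace it.

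Fourth, these outcomes are not primary, cover about a fifth of participants and follow standardised procedures. All true, and it limits the weight of the point.

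Two stronger readings are tempting and are not supported. One is that the 1.0 mm rule tolerates a 1.0 mm bias per fold, hence 4 mm on the sum. The rule triggers a repeat when two readings disagree; it neither permits nor bounds bias, so the article gives no basis for that size. The other is that the step test is equally exposed. Bench height follows the test manual, pace a metronome and heart rate a monitor; exertion is reported by the participant, and software computes the result.

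**Conclusion.** The point holds as an avoidable risk of detection bias in skin folds and waist. It rests on a stated choice to leave researchers unblinded and on the absence of any described masked assessor. That these readings are in fact taken unmasked is an inference.

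The size is conditional. With 177 v 82, an assumed SD of change of 10 to 20 mm and an assumed 2 mm differential shift in the change, the false-positive rate is about 32% to 12% instead of 5%. It falls to about 12% to 7% if the effective shift is 1 mm, and to 5% if the bias is the same at both visits or absent. These figures show how sensitive the comparison is; they are no evidence that a bias occurred. A reader might infer that the trial's main result is compromised. The article does not support that, because measured weight comes from a digital scale and is little affected.

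**What to change.** At the six- and 24-month visits:

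1. Have the same staff take skin folds and waist from appointment lists and forms that carry only the participant number, with no arm and no earlier readings.
2. Ask participants on arrival not to mention their programme.
3. Keep counselling records away from the measuring staff.
4. Have the assessor record, for each participant, whether the arm became known.
5. State in the protocol who takes these readings and that they are masked as far as possible.

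Report the record in item 4 descriptively, or use it in a cautious sensitivity analysis only. Participants whose arm stayed unknown form a subset selected after randomisation, so a comparison within it is not protected by randomisation.

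The cost is reprinted forms and one instruction, with no extra staff and no change to treatment. Masking will be partial, since some participants will reveal their arm. The sub-sample baseline readings were taken after randomisation and cannot be masked retrospectively; report this as a limitation.

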### Study groups

#### Control group

The employees in the control group received three information brochures with general information on overweight, physical activity and nutrition, and a calorie chart. These materials were briefly explained to the employee. All materials were published by the Netherlands Heart Foundation, for general use.

#### Intervention groups

Both intervention groups received a lifestyle intervention programme. This intervention was similar in content, but differed in the way the content was distributed to them and in the way the participant communicated with a personal counsellor that was appointed to them. The intervention conditions are described later on.

### Participant flow

The study design and participant flow (achieved at recruitment closure and brought up to closure of the baseline measurement period, August 2004) are shown in Figure 1.

Out of a total of approximately 21,000 employees, 4,619 returned the screening questionnaire. Of these, 2,615 were eligible and had no objections to receiving further information. They received an information brochure in which the study protocol was clearly described. Employees were free to further inquire about the study without any engagement. 1,454 employees were willing to participate and applied in time. They were all individually invited for a first appointment in which the basic measurements body weight and body height were assessed by the researchers. From these measurements, BMI was calculated. Those with a BMI lower than 25 kg/m^2^, which was the case for nine employees, were excluded. One employee became pregnant between screening and baseline measurements and was also excluded. One employee withdrew before randomisation. 57 employees did not show up for the baseline measurements. Therefore, 1,386 employees were randomised to the two intervention conditions (phone group N = 462, internet group N = 464), or to the control group (N = 460). Within these groups a number of subjects received additional measurements as follows: phone group N = 91, internet group N = 93 and control group N = 92. A second appointment was arranged within one week after randomisation, to perform these measurements. In each group a few employees were unable to attend the additional measurements: five out of the phone group, two out of the internet group, and ten out of the control group.

